| 6.Methods:  a) Subject numbers: How many local subjects? 30 How many total subjects? 30  *b) Major Inclusion/Exclusion Criteria:*  All patients must meet the following pre-established inclusion criteria (Lun et al., 2005; Stefanyshyn et al., 2006). These will be assessed by a sports medicine physician prior to beginning testing.  **History:** (1) Nontraumatic unilateral and/or bilateral peripatellar or retropatellar knee pain; (2) Patellofemoral knee pain with and/or after activity; (3) Inactivity patellofemoral pain and/or stiffness, especially with sitting with knees held in flexed posture; (4) No history of knee surgery; **Physical examination:** (1) No or minimal articular or periarticular effusion or bursitis; (2) No significant joint line tenderness; (3) No intra-articular ligamentous instability; (4) Peripatellar tenderness ± mild inferior patellar pole tenderness; (5) No patellar apprehension; **Other:** (1) Between the age of 18 and 45; (2) Run at least 15 km per week regularly; (3) do not have any other medical conditions; (4) are not participating in any other PFPS treatment; (5) Are heel-toe runners  *c) Interventions: (What will be done to the subjects and for how long?)*  **PILOT TEST:** 10-16 healthy subjects will be recruited internally at the Human Performance Lab to pilot test 8 footwear conditions (±3, ±6, ±9 degree orthotic wedge inserted into the neutral shoe [+=medial. - = lateral; these are standard wedge angles, eg, Fisher et al., 2007]; an off-the shelf adidas ForMotion running shoe (allows slight relative movement at the heel of the shoe between the foot and outsole), and an off-the-shelf adidas shoe with ForMotion restricted [this is the neutral condition]). All shoes are displayed on a separate attachment for this application. Subjects will be asked to run at 4 m/s during 5 motion analysis trials with each shoe condition (i.e. 40 trials total). Order will be randomly assigned. In motion analysis trials, reflective markers are attached to anatomical landmarks of the lower extremity. Subjects run over a force platform while infrared cameras record marker trajectories. The 3D positions of the markers are coupled with the ground reaction forces recorded from the force plate, and through a series of inverse dynamics calculations we are able to indirectly determine forces in the knee joint. Specifically, we are interested in the footwear that can most significantly reduce knee abduction moments. The footwear that shows the best optimization between the mechanical benefit just described, and shoe comfort will be chosen as the intervention condition in the following experiment. The test should take between 1.5-2.5 hours per subject. **PFPS STUDY**: 30 patients with PFPS will be asked to perform 10 motion analysis trials in a laboratory setting. The motion analysis procedure will be the exact same as described in the above pilot test. Of these 10 trials, 5 will be with the intervention shoe determined from the above pilot test, and 5 will be with the neutral running shoe described above. Order will be randomly assigned. One or two more trials/conditions may or may not be added if we find multiple shoes may be of benefit from the pilot test results. The total laboratory setting testing should take 1.5-2.5 hours per subject. Half of the patients will then be given the neutral shoe and the other half will be given one (only one) of the experimental shoes to take home and use when running on a regular basis for six weeks. During this time, subjects will be asked to complete weekly questionnaires which will record their current levels of knee pain and daily running mileage. At the end of the six weeks, subjects may be asked to return to the lab for a secondary motion analysis test in their experimental footwear in the event no difference was found in the first lab test, but a decrease in pain was still noted.  *d) Primary Outcome Variables (Briefly describe what will be measured and how/using what measurement tools)*  Knee joint loading will be calculated through inverse dynamics by coupling ground reaction force data from a Kistler force plate (Kistler AG, Winterthur, Switzerland) with kinematic data recorded by infrared motion analysis cameras (Motion Analysis Corp., Santa Rosa, CA). Specifically, we will look at knee abduction angular impulses (integral of the abduction moment-of-force over time) using the KinTrak program (KinTrak 7.0, University of Calgary, Calgary, AB). Subjective levels of pain will be recorded by 10cm visual analogue scale (VAS).  *e) Limitations (please list briefly any limitations you have identified in the study)*  A large amount of research is being done on PFPS patients presently at the University of Calgary, so subject recruitment may be competitive. To overcome this limitation, we will recruit subjects external from the University of Calgary as well as internally. Volunteers for our study will undergo running motion analysis testing, which may be an attractive experience for some runners, thus improving the attractiveness of this study. Secondly, although subjects will be asked to refrain from participating in any other treatment for their PFPS, such as physiotherapy, throughout the study, there is no way to actually control this. Instead, we will remind patients weekly to avoid these other treatment options, and ask patients to provide an honest account of other treatments they used during the six week study period once the study has completed. This way, we will at least be able to factor this into data analysis. |

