| --- |
| 7.Statistical Considerations in the study design:   1. *What is your sample size and how do you justify it? (Provide details of sample size calculation)*   Our sample size will be 30 subjects. No pilot test data or data from other researchers’ studies exist in regards to PFPS patient footwear interventions focusing on knee joint loading, thus power analyses cannot be properly performed at this time. However, in most biomechanical studies, a sample size between 10-16 subjects can achieve over 80% power. This is because many biomechanics studies, including the one proposed in this application, employ a paired-samples statistical design, thereby reducing within subject error. Therefore, our planned sample size of 30 should be more than sufficient. Once testing begins, and results from 6-8 subjects are known, full power analyses will be conducted to ensure over 80% power will be reached through 30 subjects. Sample size will be adjusted accordingly.   1. *Data Analysis (Which method of analysis will you use?)*   As mentioned above, the study will use a paired-samples design. Each subject’s motion analysis experimental condition will be compared against their own neutral condition. Thus a paired-samples t-test (a=0.05) will be used here. In the second part of the study, where subjects are asked to run on their own for six weeks, their initial pain score data will be used as a baseline for comparison to their final pain score. Thus, a paired-samples t-test (a=0.05) will be used here as well. |

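### The laboratory shoe comparison randomises shoe order, but the stated paired t-test does not use it; stating, balancing and modelling the order would be a cheap gain in precision

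*Protocol*

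**What the plan says.** Protocol section 6c (PFPS study) sets up a within-patient comparison: "30 patients with PFPS will be asked to perform 10 motion analysis trials in a laboratory setting". Half of the trials are in the intervention shoe, and for the other half the text reads "5 will be with the neutral running shoe described above. Order will be randomly assigned". It does not say whether the thing ordered is a block of five trials in one shoe or each single trial. It also does not say whether the orders are balanced across patients. On session length it says "The total laboratory setting testing should take 1.5-2.5 hours per subject", and it leaves room for further conditions: "One or two more trials/conditions may or may not be added if we find multiple shoes may be of benefit from the pilot test results".

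Section 7 (Data Analysis) fixes the test. Each patient's experimental condition is "compared against their own neutral condition. Thus a paired-samples t-test (a=0.05) will be used here". No order or period term is mentioned.

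The inclusion criteria in section 6b require "2) Patellofemoral knee pain with and/or after activity".

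**The concern.** Both shoes are run in one session by patients selected for pain with or after activity. Something may therefore change between the first and the second shoe: the patient warms up, tires, becomes used to the task or hurts more. If the shoes are run as blocks, the design is a two-period crossover. Each patient's difference is then the shoe effect plus or minus the first-to-second shift, with the sign set by the order.

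A paired t-test that leaves the order out treats this known alternation as noise. The cost is precision in the test of the first primary objective (knee loading). In addition, if the orders happen to split unevenly, part of the shift stays in that trial's estimate.

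**Working it through.** **Inputs from the protocol.** n = 30; paired t-test at alpha 0.05 (sidedness not stated, two-sided assumed); five trials per shoe.

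**Inputs not in the protocol, assumed here.** The paired effect in SD units (dz), and the shift π, defined as second block minus first block in units of the drift-free SD of the paired difference. The range tried for π is 0 to 1, the same for every patient unless stated otherwise.

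**The plan's own figure.** Section 7 says that 10-16 subjects usually give over 80% power, so 30 should suffice. No effect size or SD is given, so this cannot be reproduced. Working backwards with the noncentral t distribution, 80% power needs dz = 0.996 at n = 10, 0.749 at n = 16 and 0.529 at n = 30.

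**Model with shoes in blocks.** D_i = δ + o_i·π + e_i, where o_i = +1 if the experimental shoe is run second and −1 if first, and e_i has SD 1.
- Variance seen by the plain t-test under independent random order: 1 + π². This is 1.06, 1.25 and 2.00 at π = 0.25, 0.5 and 1.
- Displacement of the estimate in a given trial: π·(n1 − n2)/n, where n1 and n2 count the two orders.

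**Power at n = 30, dz = 0.529** (simulation, 100,000 trials per cell):

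| Order and analysis | π = 0 | 0.25 | 0.5 | 1 |
|---|---|---|---|---|
| Independent random order, plain t-test | 80% | 78% | 71% | 50% |
| 15:15 order, plain t-test | 80% | 78% | 72% | 50% |
| Independent random order, order term | 79% | 79% | 79% | 79% |
| 15:15 order, order term | 80% | 80% | 80% | 80% |

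Balance alone removes the displacement but does not recover the power; the order term does.

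**Uneven splits, if each order were an independent coin toss.** An exact 15:15 split has probability 14%. A split of 18:12 or worse has probability 36% (displacement at 18:12 is 6/30 = 0.20π), and 20:10 or worse 10% (at 20:10, 10/30 = 0.33π). The mean absolute displacement is 0.14π.

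**Validity.** With no shoe effect, the plain t-test rejects in 4.9-5.0% of trials at every π when averaged over the randomisation, and the mean estimate is about 0. Given a realised 20:10 split, it rejects in 6.6%, 10.1% and 17.4% at π = 0.25, 0.5 and 1. Given 15:15, it rejects in 4.3%, 2.9% and 0.6%.

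**If single trials are ordered at random.** Under linear drift over the 10 trials, the SD of the position contrast is 0.382 of the block contrast, so the variance factor is 1 + (0.382π)²: 1.01, 1.04 and 1.15. Power at dz = 0.529 is then 79.6%, 78.4% and 74.3% at π = 0.25, 0.5 and 1.

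**If the shift varies between patients.** With blocks, 15:15 order, mean shift 0.25 and between-patient SD 0.5, power is 69% with the plain t-test and 71% with an order term. The term removes only the common part: the variance goes from 1 + 0.0625 + 0.25 = 1.3125 to 1.25.

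**If the effect is larger.** At dz = 0.749 with blocks and independent random order, the plain t-test has 98%, 97%, 94% and 80% power at π = 0, 0.25, 0.5 and 1.

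**The case against.** The strongest reply is that nothing stated is wrong. Random order is itself the protection against drift, and the calculations confirm that the test keeps its level and the estimate is unbiased on average. That stands. A reader might infer a systematic bias in the loading estimate; the documents do not support this. The displacement belongs to a particular uneven allocation and averages to zero.

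A reader might also infer that the orders are left unbalanced. The protocol only fails to say that they are balanced. Random assignment does not exclude a balanced list, and such detail may sit elsewhere, so the split probabilities hold only under independent tosses.

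The size of the loss is also open. The protocol gives neither direction nor size for a shift, and does not link pain within the session to the abduction impulse. The task is 10 runs by people who run at least 15 km a week. The same session length is quoted for the 40-trial pilot, so it says little about fatigue. If trials are ordered singly the loss is slight, and if the effect is as large as section 7 presumes there is power to spare. The planned power check after 6-8 subjects would see any order variance in the observed differences, though so few subjects estimate it poorly.

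It is tempting to extend the point to the eight-shoe pilot. The pilot subjects are healthy, so the pain argument does not apply. The shoe is chosen on comfort as well as loading, and chance differences in run position cannot be turned into a loading error from anything in the documents. That extension is not made.

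What survives is that section 7 names the test, that test discards the randomised order, and a better analysis costs almost nothing.

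**Conclusion.** A minor point on efficiency and clarity, not an error of validity. If the shoes are run as blocks and the shift is common to all patients, the plain paired t-test loses about 2, 9 and 30 percentage points of power at assumed shifts of 0.25, 0.5 and 1.0 SD (n = 30, dz = 0.53). An order term with 15:15 allocation keeps about 80% throughout. The gain is smaller if trials are ordered singly, if the shift varies between patients, or if the true effect is well above 0.53 SD. Since the protocol gives no effect size, SD or shift, neither the loss nor spare power can be taken as established.

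**What to change.** In section 6c, state whether order is assigned to shoe blocks or to single trials, and balance it across the 30 patients. With two shoes in blocks this means 15 neutral-first and 15 experimental-first; if conditions are added, use a balanced set of sequences.

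In section 7, include order in the laboratory analysis. With two shoes in blocks, analyse the paired difference with an order term, so that the shoe effect is the mean of the two order-group mean differences, on 28 degrees of freedom instead of 29. If trials are ordered singly or conditions are added, use a patient-level mixed model with run position or period.

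The cost is a sentence or two in each section and, in the two-shoe case, one degree of freedom. With no drift and 15:15 order, power is still about 80%. No patients or trials are added.

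### The number of experimental shoes is left open after the pilot, while the analysis provides one loading test at 0.05 and does not say whether one or several designs go home

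*Protocol*

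**What the plan says.** Section 6(c) describes a pilot of eight footwear conditions in 10–16 healthy runners. The condition with the best balance of mechanical benefit and comfort becomes the intervention shoe. In the patient study, 30 runners each complete ten laboratory trials, five in that shoe and five in the neutral shoe. The same section then allows an extension: "One or two more trials/conditions may or may not be added if we find multiple shoes may be of benefit". For the six-week phase, half the patients get the neutral shoe and "the other half will be given one (only one) of the experimental shoes to take home". Section 5 says that the choice between the neutral and an experimental shoe is randomised and that patients are blinded to it.

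Section 7 is written for one experimental shoe. It states "Our sample size will be 30 subjects" and, for loading, "Each subject’s motion analysis experimental condition will be compared against their own neutral condition", followed by "Thus a paired-samples t-test (a=0.05) will be used here". For pain, the final score is compared with the patient's own baseline: "Thus, a paired-samples t-test (a=0.05) will be used here as well". A power check after 6–8 subjects may change the sample size, but it is not tied to the number of shoes.

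**The concern.** How many interventions a trial has, and which patient receives which, are matters of design. Section 6(c) leaves both open, and Section 7 does not follow it.

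For loading, the first objective in Section 4 asks whether a footwear intervention can lower knee loading. With one shoe, one test answers it. With two or three shoes and no primary one named, nothing prevents a single favourable result among several unadjusted tests from being presented as the answer.

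For pain, if several experimental designs go home, the experimental half is a mixture. A fall in pain could then not be credited to a particular shoe. Section 5 also plans to relate change in loading to change in pain, and that relation would be harder to interpret with different shoes in the same half.

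**Working it through.** **1. The plan's own figure.** Section 7 justifies 30 patients by stating that 10–16 subjects usually give over 80% power in paired biomechanical designs. No effect size or SD is given, so the figure cannot be reproduced. It can only be back-solved. For a paired t-test (two-sided 0.05; sidedness is not stated, so this is assumed), power = P(T > t(0.975, n−1)), where T is noncentral t with n−1 degrees of freedom and noncentrality d√n. Setting power to 80% gives:
- n = 10: d = 1.00
- n = 16: d = 0.75
- n = 30: d = 0.53

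These all refer to one comparison.

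**2. Number of loading tests.** One intervention shoe plus one or two more gives k = 2 or 3 experimental shoes, each against the same neutral shoe in the same 30 patients.

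**3. Family-wise error if each test is run at 0.05.**
- If the tests were independent, the error is 1 − 0.95^k. For k = 2 this is 1 − 0.9025 = 9.75%. For k = 3 it is 1 − 0.857375 = 14.3%.
- The tests share the neutral condition. If each shoe's measurement has equal and independent variation around the patient's own level, each shoe-minus-neutral difference has variance 2 (in units of that variation) and two differences have covariance 1, so their correlation is 1/2 = 0.5. Simulating k paired t-tests with n = 30 under the null (200,000 runs) gives 9.0% for k = 2 and 12.7% for k = 3. A separate simulation gave 9.1% and 12.5%.
- The documents give no correlation. At correlation 1 the tests coincide and the error is 5%. At zero it is close to the independent values. The range is therefore 5–9.75% for two shoes and 5–14.3% for three.

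**4. Cost of adjusting.** An equal split of alpha gives 0.05/2 = 0.025 or 0.05/3 = 0.0167 per test. At n = 30 and 80% power, the detectable loading effect rises from d = 0.53 to 0.59 or 0.62.

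**5. The take-home phase.** Half of 30 is 15. The wording on the take-home shoe allows two readings:
- One experimental design is carried forward for the whole half, and all 15 wear it.
- Each patient gets one shoe from a set of two or three, and the designs differ between patients. An equal split, which is an assumption, gives groups of 7 and 8, or three groups of 5.

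Section 5 randomises neutral against experimental under either reading. It does not say how a patient is assigned among several experimental shoes, which matters only under the second reading. If pain were then tested within each shoe, the formula in step 1 gives a detectable paired change of d = 0.78 at n = 15, 1.16 at n = 8, 1.27 at n = 7 and 1.68 at n = 5. Section 7 plans no such analysis by shoe, so these figures show only what a later attempt to separate the shoes would face.

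**The case against.** The extra conditions are optional and depend on a pilot in separate healthy runners. The number of shoes can therefore be known before any patient is measured, and choosing shoes in the pilot does not inflate the error in patients. A rule for multiple tests could also sit in a statistical analysis plan that is not shown. Both points stand. They do not remove the mismatch within the Protocol: Section 6(c) allows up to three experimental shoes without saying when that choice closes or which shoe is primary, and Section 7 states an analysis for one.

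A reader might go further in several ways that the text does not support.
- **The plan divides the experimental arm.** The wording can equally mean one design for the whole half. The budget in Section D leans that way: wedges for 15 are listed only as an alternative to using the existing shoe.
- **A loss of power for pain by shoe, or between arms.** Section 7 plans only a comparison of baseline with final score, and allows the sample size to be revised.
- **Investigators may match shoe to laboratory response.** Section 5 says that the take-home shoe is randomised. It is silent only on assignment among several experimental shoes.
- **Shoes with opposite wedge directions could be pooled.** Both directions are piloted, but shoes are selected for reducing abduction moments with acceptable comfort, and nothing suggests that opposite wedges would both qualify.
- **The pilot uses the wrong outcome.** The pilot text says "we are interested in the footwear that can most significantly reduce knee abduction moments" and Section 6(d) says "Specifically, we will look at knee abduction angular impulses". The impulse is the moment integrated over time, so the first phrase can be general wording for the same loading. It is worth stating the selection measure, but this is not a contradiction.
- **Any one positive shoe counts as success.** No such rule is stated. The difficulty is that none is stated that would exclude it.

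**Conclusion.** The point holds in conditional form. If the option is used and every shoe is tested at 0.05 as Section 7 is written, the family-wise error for the loading objective is about 9% with two shoes and 12.5–12.7% with three, against 5% for one. This rests on two-sided tests, a shared neutral condition and a correlation of 0.5 between differences. If the option is not used, the loading test stays at 5%.

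For the pain phase, the fault is ambiguity and not a demonstrated loss. The Protocol does not say whether one or several designs go home, or how patients would be assigned among several. If the half is divided, a pooled pain result cannot be attributed to any one shoe. If it is not divided, the group of 15 is intact.

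**What to change.** After the pilot and before the first patient is enrolled, amend Sections 6(c) and 7 to state:

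1. The number of experimental shoes to be run in the laboratory.
2. One named primary experimental shoe, chosen on the pilot's mean reduction in knee abduction angular impulse together with comfort.
3. That this shoe alone is randomised against neutral for the six weeks, and that it alone is the subject of the 0.05 loading test.
4. That any further laboratory shoe is a secondary condition with Holm correction and cannot by itself satisfy the loading objective. That last clause is needed because Holm makes no adjustment when there is only one secondary test.

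If the investigators prefer to treat all shoes as equal for loading, splitting alpha across them would also work, at the small cost shown in step 4. The statement on the take-home shoe would still be needed.

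The change needs protocol wording only and no extra patients. The downside is that a second promising shoe is not tested for pain in this trial.

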| 5.Basic Study Design (Briefly describe your study):  Patients will be asked to run across a force platform (which measures ground reaction forces) while high speed cameras record body segment trajectories through space. Together, these data will allow us to noninvasively calculate internal forces at the knee joint. Each patient will be asked to perform trials with a neutral and experimental shoe conditions so that we can determine whether the experimental footwear reduces knee joint loading for PFPS patients. Then, each subject will receive either the neutral or an experimental shoe (this will be randomized and blinded for the patients) to take home for six weeks. The subjects will be asked to continue their training protocol and run on a regular basis with the shoe provided while knee pain levels and running mileage are subjectively monitored. At the end of the study, we will be able to determine if a decrease in knee joint loading is correlated with a decrease in knee pain. |

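### The only stated pain test is a before/after paired t-test, so the randomised neutral-shoe arm serves as comparator in no stated pain test and general improvement can be read as a shoe effect

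*Protocol*

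**What the plan says.** Protocol section 5 (Basic Study Design) sets up a randomised, patient-blinded take-home phase: "each subject will receive either the neutral or an experimental shoe (this will be randomized and blinded for the patients". Section 6c (Interventions) gives the split: "Half of the patients will then be given the neutral shoe and the other half will be given one (only one) of the experimental shoes". Pain is recorded on a 10 cm VAS, with follow-up of six weeks.

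Section 7 (Data Analysis) first assigns a paired t-test to the laboratory comparison, in which every patient runs in both shoes. For the take-home phase it then says that "their initial pain score data will be used as a baseline for comparison to their final pain score", and concludes: "Thus, a paired-samples t-test (a=0.05) will be used here as well". It does not say whether this test is run on all 30 patients together or within each arm. No comparison of pain, or of pain change, between the arms is stated anywhere.

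The sample-size text in section 7 rests on pairing as well. It states that "in most biomechanical studies, a sample size between 10-16 subjects can achieve over 80% power", because such studies "employ a paired-samples statistical design, thereby reducing within subject error". Section 5 also expects to relate the decrease in loading to the decrease in pain by a correlation, but section 7 gives no method for it.

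**The concern.** Pairing suits the laboratory part because each patient is measured in both shoes, so the within-patient difference is the shoe contrast. In the take-home part each patient wears one shoe only, and the within-patient difference is a change over time. That change contains any shoe effect plus everything else that moves pain over six weeks.

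The Protocol itself points to several such influences. Section 6e concedes that use of other treatments cannot be controlled. Section 8 has physicians present the study as a possible treatment, which can raise expectations. Mileage is monitored because it may vary. The neutral arm and the blinding are there to balance these influences, yet the stated test does not draw on them.

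At stake is the pain objective, one of two primary objectives. A significant fall in pain under the stated analysis could not be attributed to the shoe, although the trial randomises and could support that inference.

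**Working it through.** **Inputs from the Protocol.** N = 30 (section 7); half per shoe group, so 30/2 = 15 per arm (section 6c); alpha 0.05 (section 7). Sidedness is not stated; two-sided is assumed. No effect size, SD or rate of natural improvement is given, so effects are expressed in SDs of the pain change.

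**The plan's own figure.** N = 30 cannot be reproduced, because no effect size lies behind it. Solving backwards for 80% power, a paired test needs a standardised effect of 0.996 at n = 10, 0.749 at n = 16 and 0.529 at n = 30.

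**Step 1: the paired test when the shoe does nothing.** Let r be the mean general improvement divided by the SD of change. The test statistic follows a noncentral t distribution with n − 1 degrees of freedom and noncentrality r√n. The probability of significance is the area beyond ±t(0.975, n − 1). For r = 0.5 the noncentrality is 0.5 × √15 = 1.94 in one arm and 0.5 × √30 = 2.74 pooled.

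| r (assumed) | one arm, n = 15 | pooled, n = 30 |
|---|---|---|
| 0 | 5% | 5% |
| 0.25 | 15% | 26% |
| 0.5 | 44% | 75% |
| 0.75 | 77% | 98% |
| 1.0 | 95% | about 100% |

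On the VAS, a general fall of 1.0 cm with an SD of change of 2.0 cm gives r = 1.0/2.0 = 0.5. A fall of 0.5 cm with SD 2.5 cm (r = 0.2) gives 11% at n = 15, and a fall of 1.5 cm with SD 1.5 cm (r = 1.0) gives 95%. All these VAS values are assumptions.

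**Step 2: a between-arm test in the same setting.** General improvement common to both arms cancels, so the error rate stays at 5%. A simulation of 100,000 trials at r = 0.5 gave 4.9% for the two-sample test on change, against 44% (one arm) and 76% (pooled) for the paired test.

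**Step 3: does comparing two per-arm verdicts help?** The arms are independent. At r = 0.5, the chance that the experimental arm is significant and the neutral arm is not is 0.438 × (1 − 0.438) = 0.246, or 25%. The chance that exactly one arm is significant is 2 × 0.246 = 0.49. So it does not help.

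**Step 4: what 15 per arm can detect.** For a two-sample t-test on change with true difference d in SDs of change, the noncentrality is d√(n/2) with 2n − 2 degrees of freedom. At n = 15, 80% power needs d = 1.06 (noncentrality 1.06 × √7.5 = 2.90). A paired test needs 0.53 on all 30 or 0.78 on one arm.

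| True difference (SD of change) | power, 15 per arm | n per arm for 80% |
|---|---|---|
| 0.53 | 29% | 57 |
| 0.75 | 51% | 29 |
| 1.0 | 75% | 17 |

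These are unadjusted figures. ANCOVA may recover some power, depending on the correlation between baseline and final VAS, which the Protocol does not give.

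**The case against.** The strongest defence is that the paired test matches the wording of the second hypothesis in section 4, which expects pain to fall over six weeks, and that the second objective asks whether lower loading goes together with less pain. Read literally, that is a within-patient change plus an association, and section 5 does foresee a correlation. This stands in part: a between-arm test estimates the shoe's effect on pain and would not by itself show that reduced loading goes with reduced pain. But the paired test uses neither loading nor allocation, so it does not answer that question either.

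A reader might infer that the neutral arm plays no part in the pain data at all. The text does not support this. Neutral-arm patients may enter a pooled or per-arm paired test, or the correlation. What holds is that they are not a comparator in any stated pain test.

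A reader might also infer that recruitment at diagnosis guarantees regression to the mean. Section 8 lists three routes, and the third is posters in athletic facilities and sports medicine offices. Section 6b sets no minimum pain score, and section 3 describes the condition as chronic. Spontaneous improvement is plausible but not documented.

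Deferral to a statistical analysis plan is a weak defence, because section 7 itself names the contrast, the test and the alpha.

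**Conclusion.** The point holds: for a randomised two-group phase, the Protocol fixes a pain analysis that does not use the randomised contrast. Improvement unrelated to the shoe can then be read as a shoe effect. Whether it will be is not something the document shows.

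The size depends on assumptions. With no general improvement the paired test keeps its nominal 5%. With 0.25 to 1.0 SD of general improvement and no shoe effect, it is significant in 15% to 95% of trials at n = 15, and in 26% to about 100% if all 30 are pooled. These figures illustrate the risk and are not expected error rates for this trial. They assume normally distributed changes, two-sided testing, no dropout and the same general improvement in both arms.

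A second consequence needs no assumption about improvement. The pairing argument for N = 30 applies to the laboratory loading comparison only and does not carry over to a between-arm pain comparison.

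**What to change.** In section 7, replace the second paired t-test by a comparison of the arms as randomised. One suitable form is ANCOVA of the week-6 VAS on arm with baseline VAS as covariate, reporting experimental minus neutral with a 95% CI. A two-sample test of change would also use the randomisation. Section 6c leaves room for more than one experimental shoe, so state that these are pooled against neutral in this comparison. Keep within-arm changes as description, and list the loading–pain correlation from section 5 as a separate analysis.

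Restate the sample-size text as well. Limit the paired-design argument to the laboratory loading comparison. For pain, state that 15 per arm gives 80% power only for a difference of about 1.06 SD of change, unadjusted. Section 7 already plans a power analysis after 6-8 subjects with adjustment of the sample size; it should cover the between-arm pain comparison too.

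The cost is a rewritten analysis sentence and a revised sample-size paragraph, with no new data items. The downside is that the stated sensitivity for pain becomes less favourable, and N may have to be reconsidered if a smaller difference matters.
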